## Abstract

**Background:**

Although the relationship between *deqi* sensations and curative effect has always been controversial, *deqi* sensations has been regarded as the key indicator of clinical efficacy of acupuncture therapy. There is little evidence for standardization or visualization of the mechanism of acupuncture’s therapeutic effect. This trial aims to evaluate the effect of needling at Zusanli (ST36) on antral contraction function as visualized by ultrasound.

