## Introduction

### Background and rationale {6a}

Acupuncture is an ancient medical technique in China with a history of more than 2000 years [1]. Acupuncture therapy involves the insertion of a needle into the body at specific points to prevent or treat various diseases. Although the mechanism of acupuncture remains unclear, its therapeutic benefit has been approved by many western countries and is used as complementary and integrative medicine globally [2–4]. This is exemplified by the fact that Chinese acupuncture was included in the representative list of Intangible Cultural Heritage of Humanity in 2010.There were more than 4000 registered medical practitioners in the Chinese Medicine Board of Australia (CMBA) by 2014 [5]. Acupuncture is also an integral component of conventional therapy in the UK, with approximately 4 million acupuncture treatments having been provided in 2009 alone [6]. In the USA, 6.8% of 22,512 adults reported they will use acupuncture for life [7] and between 2002 and 2012 the number of acupuncture users and licensed acupuncturists increased by 50% and 100% respectively [8].

Traditional Chinese medicine (TCM) merges with naturalistic theories, philosophy, and other alternative disciplines. The common ideology holds that qi is the primary substance and inherent motivation of life. This life force is distributed in the viscera and meridians to promote and stimulate the physiological activities of human body. According to TCM theory, the dysregulation of qi movement is the root cause of diseases. *Deqi is* a complicated sensory composite that accompanies needling stimulation. The onset of deqi is considered a vital phenomenon of acupuncture treatment that determines clinical efficacy. The sensation was first documented in Huang Di’s Canon [9]. Although acupuncture practitioners realize the dominant role of *deqi* in achieving a positive clinical outcome [10–12], and it is taken as a key parameter in many acupuncture studies, current clinical research evidence is insufficient to prove the interaction between *deqi* and clinical value [13–16]. Both wrist-ankle acupuncture (WAA) therapy and Fu’s subcutaneous needling (FSN) therapy are without obvious *deqi* sensation, but still have a curative effect [17, 18].

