### Objectives {7}

Participants who are in acupuncture with the *deqi* sensations group will experience more dramatic changes in the antral contraction frequency (ACF), antral contraction amplitude (ACA), and skin temperature of abdomen than those in the acupuncture group without *deqi* sensations.

The objectives include the following:
To determine the effects of ultrasound-guided acupuncture at ST36 on the antral contraction frequency, the antral contraction amplitude, and the skin temperature of the abdomen.To observe and analyze the relationship among the acupoint, the anatomical structure of acupoint area, and the antral contraction function in the  acupuncture group (with *deqi*) and sham acupuncture group (without *deqi*) respectively.To provide standardized and visualized experimental basis for improving the safety and effectiveness of clinical acupuncture techniques.

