## Interventions

### Explanation for the choice of comparators {6b}

In order to comply with the proposed objectives and verify whether depth and intensity of acupuncture will affect the motility of gastric antrum, we take the intervention of shallow acupuncture at ST36 as a way of contrast to distinguish from routine acupuncture. The sensations generated by shallow acupuncture are very slight but is similar to the feeling of true acupuncture. Furthermore, to a great extent, it ensures that the participants cannot distinguish the group distribution in appearance, which is beneficial to blind method implementation.

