### Intervention description {11a}

All participants are asked to abstain from eating for at least 2 h before the trial. Participants in both groups will receive acupuncture on the right-sided ST36. A thermal infrared imager detects the thermal infrared spectrum of the gastric area skin and observes the antral contraction by ultrasonography.

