#### Sham acupuncture group

Participants in the sham acupuncture group will be punctured at ST36 with the needle tip reaching no deeper than the superficial fascia and without any needle manipulations. The remaining procedures and recording details are the same as those of the acupuncture group.

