### Sample size {14}

The sample size was estimated using the Power Analysis and Sample Size (PASS version 15) software. According to our pilot trial, we anticipate that the change in the frequency of antral contraction will be more pronounced in the acupuncture group than in the sham acupuncture group and that we will detect a difference of 30% between effective rates in the 2 groups (70% in the acupuncture group compared with 40% in the sham acupuncture group). On the basis of a 2-sided alpha level of 0.05 and a power level of 90% with a 10% dropout rate, we calculated that our trial will require a sample of 116 participants (58 in each group).

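### The stated aim, Objective 1 and the expected conclusions go beyond the randomised comparison, which isolates only deep, manipulated versus shallow, unmanipulated needling at ST36

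*Protocol article*

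**What the plan says.** The broad question appears in four places in the protocol article:

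- Abstract, Background: "This trial aims to evaluate the effect of needling at Zusanli (ST36) on antral contraction function as visualized by ultrasound".
- Objectives {7}, first objective: "To determine the effects of ultrasound-guided acupuncture at ST36 on the antral contraction frequency", followed by contraction amplitude and abdominal skin temperature.
- Abstract, Discussion: the study may yield evidence on the safety and efficacy of manual acupuncture at this point.
- Discussion, limitations paragraph: the study is expected to give evidence on the specificity of ST36 for antral contraction.

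The design is described more narrowly. Intervention description {11a} states: "Participants in both groups will receive acupuncture on the right-sided ST36". The active arm is needled to the crural interosseous membrane and manipulated. The control arm "will be punctured at ST36 with the needle tip reaching no deeper than the superficial fascia and without any needle manipulations", and the remaining procedures are the same. Trial design {8} has two arms, allocated 1:1. Explanation for the choice of comparators {6b} says the shallow needle was chosen to "verify whether depth and intensity of acupuncture will affect the motility of gastric antrum". Statistical methods {20a} names tests between the two groups.

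**The concern.** A randomised difference removes whatever the arms share. Here they share skin penetration at ST36, so any effect of that common element cancels. What remains is the joint increment of depth and manipulation, with the deqi they are meant to produce. This is a legitimate question, but it is not the one in the abstract aim or Objective 1. Point specificity is further away still, since it would need needling at some other site.

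What is at stake is the conclusion. Taken literally, the abstract aim could turn a null difference into a statement that needling at ST36 does nothing to the antrum, even if both arms responded. A positive difference could be presented as the efficacy of needling at ST36, or as proof that this point is special, when it shows only that one way of needling it differs from another.

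**Working it through.** **1. Stated claims against what each arm supplies**

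| Claim | Comparison it needs | In the design? |
|---|---|---|
| Effect of needling at ST36 (abstract aim, Objective 1, abstract conclusion on efficacy) | Needled v un-needled, randomised | No. Both arms are needled. |
| Specificity of ST36 (Discussion) | ST36 v another site | No. Both arms use right ST36. |
| Depth, intensity and deqi (introduction, hypothesis, {6b}) | Deep, manipulated v shallow, unmanipulated at ST36 | Yes. This is the randomised contrast. |

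The un-needled people mentioned under {18b} are not a control arm. They are people who miss needling for any reason, and they are scanned to check eligibility.

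**2. Before-after change.** Contraction frequency is recorded for 10 minutes before and 10 minutes after needling, so within-arm change is measured. Participants have not eaten for at least 2 hours, lie supine, and may not eat, drink or leave the bed during the study. Elapsed time, longer fasting, posture and expectation all run alongside the needle, and no arm shows what they do alone.

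**3. What the sample-size figures refer to.** Sample size {14} assumes effective rates of "70% in the acupuncture group compared with 40% in the sham acupuncture group", two-sided alpha 0.05, power 90% and 10% dropout. With the unpooled two-proportion formula:

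n per arm = (1.960 + 1.282)² × (0.7×0.3 + 0.4×0.6) / 0.3² = 10.507 × 0.45 / 0.09 = 52.54

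52.54 / 0.9 = 58.4, in line with the stated 58 per arm (116 in total). Rounding up at each step instead gives 53, then 59 per arm (118). Either way, the 30 points are deep minus shallow at the same site.

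**4. Illustration only: effect against no needling.** The plan gives no un-needled rate; call it p0 and assume values:

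| Assumed p0 | Deep v none (70 − p0) | Shallow v none (40 − p0) | Trial contrast |
|---|---|---|---|
| 0% | 70 | 40 | 30 |
| 10% | 60 | 30 | 30 |
| 20% | 50 | 20 | 30 |
| 30% | 40 | 10 | 30 |
| 40% | 30 | 0 | 30 |

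The trial contrast is the same in every row, so it carries no information about which row is true.

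**5. Illustration only: a partly active shallow needle.** Assume 40% un-needled and 70% with deep needling, and let the shallow needle produce a share s of that 30-point effect, so that its rate is p2 = 0.40 + 0.30s. With p1 = 0.70 and m the mean of the two rates,

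power = Φ{[(p1 − p2)√n − 1.96√(2m(1 − m))] / √(p1(1 − p1) + p2(1 − p2))}

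with n = 58, or 52 after 10% dropout:

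| s | Shallow rate | Power, n = 58 | Power, n = 52 |
|---|---|---|---|
| 0 | 40% | 0.91 | 0.88 |
| 0.5 | 55% | 0.38 | 0.35 |
| 1 | 70% | 0.025 | 0.025 |

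The last row is the error rate in the direction favouring deep needling. In the middle row a non-significant result is the likelier outcome although both arms responded.

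**The case against.** The strongest reply is that the protocol does tell the reader what is compared. The introduction speaks of deqi and non-deqi conditions. The hypothesis that opens Objectives {7} is comparative, Objective 2 labels the arms with and without deqi, and {6b} gives depth and intensity as the reason for the comparator. The Discussion's own main objective concerns deqi, depth and effect at one point. On this view the aim is shorthand, and a null would naturally be read as no added effect of deqi.

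Much of this stands: the narrower question is present, so the defect lies in the wording of particular claims and not in a trial without an answerable question. It does not clear those claims. Objective 1 sits beside a separate objective that carries the deqi contrast, so it does not read as shorthand for it. The hypothesis also calls the control an acupuncture group without deqi, so by the protocol's own terms both arms receive what Objective 1 evaluates. The specificity claim has no support anywhere in the design.

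A reader might also infer that the protocol itself regards the shallow needle as active. It does not say so. The remark in the background that needling without obvious deqi can "but still have a curative effect" concerns two other therapies, and the 40% expected in the control arm has no cause attached to it. Activity of the shallow needle is neither stated nor excluded.

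**Conclusion.** The concern holds as a mismatch between claims and contrast. Randomisation identifies the added effect of deep, manipulated needling over shallow, unmanipulated needling at ST36. It does not identify the effect of needling at ST36 as such, and it does not test point specificity. This follows from the arm descriptions and needs no numerical assumption.

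Three stronger readings are not supported:

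- That the effect of needling cannot be estimated at all. Within-arm change is measured; the trouble is that it is uncontrolled.
- That a null result would be misread. No section says how a null will be interpreted. It could be misread if the abstract aim is taken at its word and the shallow needle is partly active.
- That the plan's figures put the effect of needling between 30 and 70 points. That range comes only from assuming an un-needled rate between 40% and 0%; the plan's own figure is the 30-point deep-versus-shallow difference.

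The power of 0.35 to 0.38 likewise rests on assumed rates, and shows only that the misreading is not far-fetched.

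**What to change.** - Reword the abstract aim, Objective 1, the efficacy statement in the abstract's discussion and the closing expectation in the Discussion, so that each refers to deep, manipulated versus shallow, unmanipulated needling at ST36. The reasoning in {6b} already supplies the sense.
- Remove the claim about the specificity of ST36.
- State that within-arm before-after changes are descriptive.
- State that the absence of a between-arm difference is not evidence that needling at ST36 has no effect on antral contraction.

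The cost is a narrower claim. Arms, procedures, outcomes, tests and the sample size of 116 are unchanged. Keeping the wider claims would need a control that this design does not have.

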**Methods:**

This is a two-arm, single-blind, randomized, controlled trial. A total of 116 acupuncture-naïve healthy subjects will be randomly allocated to the acupuncture group or sham acupuncture group in a 1:1 ratio. Participants in the acupuncture group will receive manual acupuncture at Zusanli (ST36) with the needling depth at crural interosseous membrane. Those in the sham acupuncture group will be given penetrating needling depth at the superficial fascia layer. The primary outcome will be the changes in antral contraction frequency (ACF) before and after acupuncture. The secondary outcomes will be the changes in the thermal infrared spectrum of gastric area skin, the antral contraction amplitude (ACA), the antral movement index (AMI), and the scores on the Chinese version of Massachusetts General Hospital Acupuncture Sensation Scale (C-MASS). The adverse events will be evaluated and recorded in detail.

**Discussion:**

This study may provide visual and objective evidence regarding the safety and efficacy of manual acupuncture at Zusanli (ST36). In addition, the results of this study will help to identify the role of Zusanli (ST36)in the inducing *deqi*.

**Trial registration:**

Chinese Clinical Trial Registry ChiCTR2000040686. Registered on 8 December 2020

**Supplementary Information:**

The online version contains supplementary material available at 10.1186/s13063-021-05704-9.

## Administrative information

Note: the numbers in curly brackets in this protocol refer to SPIRIT checklist item numbers. The order of the items has been modified to group similar items (see http://www.equator-network.org/reporting-guidelines/spirit-2013-statement-defining-standard-protocol-items-for-clinical-trials/).

## Introduction

### Background and rationale {6a}

Acupuncture is an ancient medical technique in China with a history of more than 2000 years [1]. Acupuncture therapy involves the insertion of a needle into the body at specific points to prevent or treat various diseases. Although the mechanism of acupuncture remains unclear, its therapeutic benefit has been approved by many western countries and is used as complementary and integrative medicine globally [2–4]. This is exemplified by the fact that Chinese acupuncture was included in the representative list of Intangible Cultural Heritage of Humanity in 2010.There were more than 4000 registered medical practitioners in the Chinese Medicine Board of Australia (CMBA) by 2014 [5]. Acupuncture is also an integral component of conventional therapy in the UK, with approximately 4 million acupuncture treatments having been provided in 2009 alone [6]. In the USA, 6.8% of 22,512 adults reported they will use acupuncture for life [7] and between 2002 and 2012 the number of acupuncture users and licensed acupuncturists increased by 50% and 100% respectively [8].

Traditional Chinese medicine (TCM) merges with naturalistic theories, philosophy, and other alternative disciplines. The common ideology holds that qi is the primary substance and inherent motivation of life. This life force is distributed in the viscera and meridians to promote and stimulate the physiological activities of human body. According to TCM theory, the dysregulation of qi movement is the root cause of diseases. *Deqi is* a complicated sensory composite that accompanies needling stimulation. The onset of deqi is considered a vital phenomenon of acupuncture treatment that determines clinical efficacy. The sensation was first documented in Huang Di’s Canon [9]. Although acupuncture practitioners realize the dominant role of *deqi* in achieving a positive clinical outcome [10–12], and it is taken as a key parameter in many acupuncture studies, current clinical research evidence is insufficient to prove the interaction between *deqi* and clinical value [13–16]. Both wrist-ankle acupuncture (WAA) therapy and Fu’s subcutaneous needling (FSN) therapy are without obvious *deqi* sensation, but still have a curative effect [17, 18].

Today, researchers have not yet reached a consensus on the relationship between *deqi*, arrival of *qi* and needling sensation. Moreover, it remains unclear whether patient’s feelings or practitioner’s perceptions are purely subjective. A large quantity of *deqi* subjectivity research is mainly focus on the scale, effectiveness, and classification of acupuncture sensations [19–22]. Objective studies of *deqi* mainly examine fMRI scans [23, 24], electrophysiology [25, 26], photoplethysmography [27, 28], energy metabolism [29, 30], and biomechanics [31, 32]. However, as mentioned above, these non-invasive techniques have failed to provide a clear understanding of the factors involved in *deqi*. In this study, we will use ultrasound imaging to understand the anatomical structure of the acupoint and its structural and functional integration and to observe the effect of acupuncture at Zusanli (ST36)on antral contraction function under *deqi* and non-*deqi* conditions respectively. This will be done with an ultimate goal to establish the relationship among structure, function, and *deqi* sensations.

### Objectives {7}

Participants who are in acupuncture with the *deqi* sensations group will experience more dramatic changes in the antral contraction frequency (ACF), antral contraction amplitude (ACA), and skin temperature of abdomen than those in the acupuncture group without *deqi* sensations.

The objectives include the following:
To determine the effects of ultrasound-guided acupuncture at ST36 on the antral contraction frequency, the antral contraction amplitude, and the skin temperature of the abdomen.To observe and analyze the relationship among the acupoint, the anatomical structure of acupoint area, and the antral contraction function in the  acupuncture group (with *deqi*) and sham acupuncture group (without *deqi*) respectively.To provide standardized and visualized experimental basis for improving the safety and effectiveness of clinical acupuncture techniques.

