#### Acupuncture group

Participants will take the supine position while wearing an eye-patch. The right calf and abdomen will be uncovered sufficiently to expose the lower border of the right patella and the space between the navel and xiphoid process respectively. The infrared imaging device will be used to measure the infrared thermal spectrum for 10 min at a lens distance of 1 m from the subject’s abdomen. Subsequently, sagittal scanning will be performed with an abdominal probe placed slightly to the right of the inferior of border of the xiphoid process. The left lobe of the liver, the lower pancreas, the abdominal aorta, and the superior mesenteric artery will be used as anatomical reference points to locate the gastric antrum. From here, the frequency of gastric antrum contraction will be recorded for 10 min continuously.

After sterilizing the skin, ST36 will be punctured at the insertion point under the guidance of ultrasonography until the needle tip reaches the crural interosseous membrane. A qualified and experienced acupuncturist will perform needle manipulation including lifting, thrusting and rotating to obtain the appropriate needling sensations (*deqi* sensation). Then, the researchers will record the frequency of antral contraction for 10 min with the ultrasonic probes and conduct needle manipulation in the 5th minute. After wiping the ultrasound gel off the skin until it thoroughly dried, the researchers will collect infrared thermal spectrum data from the abdomen.

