### Methods for additional analyses (e.g., subgroup analyses) {20b}

Not applicable. The trial has no plan for additional analyses.

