The key technical problems to be solved in this experiment are as follows: (1) the measurement of thermal infrared imaging is sensitive to ambient temperatures (2) to observe and guide the whole process of needling and obtain a legible ultrasound image of the needle body and (3) the application of the sham acupuncture method. The human skin surface temperature changes very little in a constant temperature environment. So, we will use a highly sensitive and accurate thermometer to monitor the room temperature in real time, in a closed space without convection gas or other extraneous heat source. It is necessary for the needle body to be perpendicular to the acoustic waves in order for optimal propagation. Only by using this orientation can we effectively guide the whole process of the needling. This means acupuncturists will need to penetrate into the skin at a point away from the routine insertion point. Nonetheless, we can also guarantee that the acupuncture area is located with precision. The acupuncturist and sonologist should be trained several times before the trial begins to ensure an effective implementation of the sham acupuncture technique and to be prepared to give reasonable explanations in case of doubts from sham acupuncture group participants.

There are some limitations in this randomized controlled trial. It is inevitable for acupuncturists to know when they are implementing the real or sham acupuncture treatment and its possible effects. To minimize suggestive bias from this limitation, we will ask all participants to wear an eye-mask. This trial is the primary study into the effect of a specific acupoint in relation to the *deqi* condition. In further studies, we may consider a multicenter clinical trial with patients. We expect that this study will provide more credible evidence for the effect of *deqi* sensations and the specificity of ST36 on gastric antrum contraction function and make up for the deficiency of current clinical trials focused on the methodology of acupuncture.

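### The arms are labelled by deqi but randomised as a needling package at a single point, so neither a deqi-specific nor an ST36-specific conclusion can follow

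*Protocol article*

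**What the plan says.** All references are to the protocol article.

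- **Hypothesis (Objectives {7}).** The deqi "sensations group will experience more dramatic changes in the antral contraction frequency (ACF", as well as in amplitude and abdominal skin temperature, than the group without deqi. The second objective refers to the "acupuncture group (with *deqi*) and sham acupuncture group (without *deqi*) respectively".
- **Acupuncture group.** ST36 is punctured "until the needle tip reaches the crural interosseous membrane". The acupuncturist then performs "needle manipulation including lifting, thrusting and rotating to obtain the appropriate needling sensations", and manipulates again in the fifth minute of recording.
- **Sham acupuncture group.** The needle goes "no deeper than the superficial fascia and without any needle manipulations".
- **Point needled (Intervention description {11a}).** Right-sided ST36 in both arms.
- **Comparator rationale ({6b}).** The stated purpose is to see whether needling depth and intensity affect antral motility. It adds: "The sensations generated by shallow acupuncture are very slight but is similar to the feeling of true acupuncture".
- **Deqi measurement (Secondary outcomes).** The participant scale (C-MASS, giving a MASS index) and the acupuncturist scale are both completed at the end of the session.
- **Analysis ({20a}, {20b}).** The inferential methods named are between-group t, rank-sum and chi-squared tests. On anything further: "The trial has no plan for additional analyses".
- **Wider aims.** The Background gives the ultimate goal as relating structure, function and deqi. The Discussion gives the main objective as relating deqi, needling depth and point effect, and expects more credible evidence for the effect of deqi "sensations and the specificity of ST36 on gastric antrum contraction function".

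**The concern.** The hypothesis concerns a sensation, while randomisation assigns a technique. If the two are treated as the same, a positive result will be reported as showing that deqi drives the antral response, when depth or manipulation could explain it with no role for sensation. A null result could be reported as showing that deqi does not matter, when the arms may simply not have differed enough in sensation. The Discussion also expects a conclusion about the specificity of ST36 from a trial that needles no other point. What is at stake is what the trial may conclude, not the validity of the comparison between arms.

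**Working it through.** **1. The plan's own figure.** The concern has no figure of its own, but the sample size shows which contrast the trial was sized for. Inputs from Sample size {14}: effective rates 70% and 40%, two-sided alpha 0.05, power 90%, dropout 10%. With the unpooled normal approximation:

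n per arm = (1.960 + 1.282)² × (0.7×0.3 + 0.4×0.6) / 0.3² = 52.5

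52.5 / 0.9 = 58.4 and 52.5 × 1.1 = 57.8, so about 58 per arm and 116 in total, as stated. (Rounding up at each step gives 53, then 59 per arm, or 118.) The figure is for a difference between arms. No deqi rate enters it.

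**2. What differs between the arms.**

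| Feature | Acupuncture | Sham | Set by randomisation? |
|---|---|---|---|
| Depth | interosseous membrane | superficial fascia at most | yes |
| Manipulation | yes, repeated | none | yes, always together with depth |
| Deqi | intended | slight sensation allowed | no, measured afterwards |
| Point | ST36 | ST36 | does not vary |

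**3. What the contrast identifies.** Suppose, for simplicity, that effects add: *d* for depth, *m* for manipulation, *s* for deqi, with deqi present in a share *q* of the acupuncture arm and *r* of the sham arm. Then

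arm difference = d + m + s(q − r).

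That is one estimable quantity and three unknown effects. Depth and manipulation both coincide with the arm for every participant treated as planned, so no analysis of these two arms can separate *d* from *m*. Putting the MASS index into a model that also contains arm would estimate *s* only from within-arm variation, which is not randomised, and would still leave *d + m* as a sum.

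**4. Is arm the same as deqi?** The documents do not support q = 1 and r = 0. Section {6b} describes the shallow sensation as slight but similar to true needling. Section {17a} has all participants told that feeling a sensation or not is normal. The Background also notes techniques without obvious deqi that still have an effect, which is a reason not to assume d = m = 0.

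**5. ST36 specificity.** Specificity is a contrast between ST36 and some other point. The number of arms needling another point is zero, so the trial contributes no information on it.

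**6. Illustration only.** The deqi shares below are assumed. Suppose response depended on deqi alone, at the plan's 70% and 40%. The arm rates would be 0.4 + 0.3q and 0.4 + 0.3r, differing by 0.3(q − r). Power is for a pooled-variance two-proportion test with 52 to 58 per arm (58 × 0.9 = 52.2).

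| Assumed q / r | Arm difference | Power |
|---|---|---|
| 100% / 0% | 30 points | 88–91% |
| 90% / 10% | 24 points | 70–75% |
| 80% / 20% | 18 points | 45–50% |
| 70% / 30% | 12 points | 23–25% |

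This shows how imperfect separation on sensation would dilute a pure deqi effect. It measures nothing in this trial.

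**The case against.** The strongest reply is that manipulation is the means of producing deqi, that section {6b} openly names depth and intensity as what is tested, and that comparing packages is a recognised design. All of that stands. The randomised comparison of contraction frequency, and the first objective on the effect of needling ST36, are unaffected. The fault lies in the labels and the inference.

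Four stronger readings might be inferred, and the documents do not support them:

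- *That deqi enters no analysis at all.* C-MASS is a listed secondary outcome, and section {20a} supplies between-group tests for it. What is missing from the text shown is a link between sensation and antral response.
- *That the second objective promises an analysis of deqi against antral function.* It names the acupoint, its anatomy and antral function; deqi appears there only as an arm label. The deqi relationship is stated in the Background and the Discussion.
- *That section {6b} flatly contradicts a control without deqi.* It says the sensations are very slight as well as similar, which fits an intended low-deqi control. It does not establish a deqi-free one.
- *That the dilution table sizes the problem.* No deqi rates are given, the MASS index is graded, and no cut-off for deqi is stated.

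It is also fair to say that section {20b} is headed with subgroup analyses as its example, and that a condensed article may leave detail to a fuller document. The absence of a relationship analysis is therefore claimed only for the text shown. The attribution and specificity problems do not depend on it, because they come from the arms themselves.

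**Conclusion.** The point holds as one about interpretation. Even if the plan is carried out exactly, the trial estimates the effect of deep manipulated versus shallow unmanipulated needling at ST36. It cannot assign that effect to deqi rather than depth or manipulation, and it yields nothing on whether ST36 is specific. The aim of relating deqi, structure and function has no stated analysis beyond comparisons between arms. This conclusion rests on the arm descriptions and the single point needled; it needs no assumption about how often deqi occurs. A reader might go further and infer that the primary comparison is invalid, or that one regression on the sensation score would rescue the deqi claim. Neither follows: the comparison is sound for the package, and the score is a post-randomisation measure that cannot separate the components.

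**What to change.** - **Hypothesis and conclusions.** Restate both as the effect of deep manipulated versus shallow unmanipulated needling at ST36, and drop the with/without-deqi arm labels.
- **Specificity.** Delete the expectation of evidence on ST36 specificity from the Discussion.
- **Sensation and anatomy.** Use the between-arm MASS comparison already planned as a check that the arms separated on sensation. Report any association of MASS index or measured anatomical depth with change in contraction frequency as exploratory and non-randomised, and not as evidence that separates deqi from depth or manipulation. Align section {20b} with this.

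No new arms, participants, measurements or changes to needling are needed. The cost is a narrower claim and a formal amendment: section {25} requires revision and ethics approval when the study objective changes, and the Trial status section reports that recruitment began in December 2020.
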